## Abstract

**Background:**

Domestic violence and harmful alcohol consumption are considered major public health problems worldwide. These phenomena often co-occur, and they share several risk factors. Nevertheless, few in-depth studies have supported integrated interventions for both phenomena, in particular among Latin American women. This project will study the consumption of alcoholic beverages among women and its relationship with patterns of domestic violence; furthermore, it will assess the effect of a brief intervention (BI) aimed at modifying these behaviors using a community household sample.

**Methods/design:**

This project is divided into two studies. Study 1 will employ a cross-sectional observational design and will be conducted using a household sample of adult women (approximate sample size = 1600) to assess harmful alcohol consumption and domestic violence patterns. Study 2, will be a randomized clinical trial based on specific cases from Study 1, assessing the effect of a brief intervention on women who exhibit harmful levels of alcohol consumption (AUDIT ≥ 8). Approximately 73 women will be assigned to one of two groups, either a treated group (TG) or a control group (CG). A sociodemographic questionnaire, a questionnaire concerning general health and substance use, and four other standardized instruments (i.e., the Alcohol Use Disorder Identification Test [AUDIT; used to investigate problems related to alcohol consumption], the Center for Epidemiologic Studies Depression Scale [CES-D; used to measure depressive symptoms], and the Revised Conflict Tactics Scales and Parent–child Conflict Tactics Scales [CTS2 and CTSPC; used to obtain information on violence among couples and between parents and children, respectively]) will be used to collect data.

**Discussion:**

The study protocol will employ a household survey of a representative sample from a neighborhood in a middle income country, where well-conducted household surveys remain rare. The present work represents a step toward a better understanding of violence in women’s lives and its interaction with alcohol consumption and expands the discussion on the potential strategies for public health actions seeking to prevent both domestic violence and harmful alcohol consumption.

**Trial registration:**

Brazilian Clinical Trials Registry: RBR-7rjt4t. Registered 17 October 2013.

## Background

Domestic violence and harmful alcohol consumption are two key public health problems worldwide [1]. In addition to their high prevalence, both phenomena result in considerable biological, psychological, and sociological repercussions for individuals and the general population [1, 2]. These phenomena often co-occur and share a complex set of psychosocial risk factors. However, in-depth studies aimed at supporting interventions to address both phenomena in an integrated manner remain scarce, especially among specific groups such as Latin American women.

### Alcohol consumption among women

Although alcoholic beverage consumption remains higher among men, women have significantly increased their consumption because of society’s changing gender roles [3]. According to the Global Burden of Diseases, Injuries, and Risk Factors Study in 2010 [4], alcohol consumption is the third leading risk factor for illnesses and disabilities worldwide; furthermore, the World Health Organization (WHO) considered it to be the primary risk factor for “disability-adjusted life years” (DALYs) in Tropical Latin America, which encompasses certain Latin America countries including Brazil. Depending on consumption patterns, alcohol can affect individual’s health due to accidents, dependence, liver cirrhosis, cancer, and injury. Alcohol consumption can also affect the health of other people in community and family settings, specifically due to drinking and driving situations, work absenteeism, drinking during pregnancy, and cases of violence and neglect in the parent–child relationship [2].

Previous Brazilian surveys suggest that approximately 75 % of the population has consumed alcohol at least once in their lifetime [5], and nearly 25 % of respondents reported at least one type of drinking-related problem. Furthermore, 3 % meet the criteria for alcohol abuse, and 9 % are alcohol dependent [6]. These rates varied based on gender, age, marital status, educational level, income, and country region with approximately 4 % of women abusing alcohol or being alcohol dependent [7].

It has been suggested [3] that biological factors such as lower body weight and lower fat-to-muscle ratios contribute to faster and more intense effects of alcohol among women. Compared with men, harmful alcohol consumption among women has a disproportionate effect on their lives and health, including undesired consequences regarding reproductive function and pregnancy as well as the faster development of physical, cognitive, social, and psychiatric problems [3, 8, 9].

### Domestic violence

Like alcohol consumption, violence (specifically, domestic violence) has been identified as a priority for WHO actions. Violence is a major public health problem worldwide because it has serious implications for health (in both the short and long term) as well as the psychological and social development of individuals, families, and communities [10, 11].

Domestic violence (or family violence) can be understood as “every act or omission committed by some family member in a position of power, regardless of where it occurs, which harms the well-being, physical or psychological integrity, or freedom and right to full development of another family member” [12]. Violent acts can be classified based on their type, including acts of physical, psychological, and sexual violence; alternatively, they can be expressed as forms of neglect or abandonment [11]. In the family setting, violence can occur within interpersonal relationships, including those with children, adolescents, men, women, and the elderly [13–15]. Despite the increased emphasis placed on victimized women within partnerships [11], researchers recognize that women can also be the aggressor in the marital relationship [13, 16, 17] and with regard to their children [18, 19].

Some studies suggest that domestic violence is highly prevalent and has a complex network of associations. Some of the factors associated with domestic violence include younger age, lower education level, a history of physical violence in the family, childhood sexual abuse, depression, poor socioeconomic conditions, and problems related to alcohol consumption among one or both members of the couple [20–23]. The consequences of domestic violence can be identified at different levels of life, leading to physical and psychosocial impairments. [24, 25]. Therefore, it becomes important to treat family violence as a complex phenomenon, one that tends not to be restricted to a single member of the family [22].

### Domestic violence and alcohol

Although many studies relate alcohol consumption to violent behavior, it is not possible to establish a simple and unidirectional association because of the complexity of this relationship [1, 26–29]. A population-based study in Brazil found that the aggressor was under the influence of alcohol at the time of the event in over half of the identified cases of domestic violence [14]. The literature includes several other studies that suggest an association between alcohol consumption and violent behavior among intimate partners [1, 30–35].

Although some studies have suggested that alcohol consumption is more associated with the severity of violence acts than to increases in its occurrence [31, 36], others have suggested that it should be related to both [35] and that the association between alcohol and violence becomes more powerful with increased consumption [26, 29]. To better understand how alcohol consumption might be related to a greater severity of domestic violence, it is important to consider not only the pharmacological effects of alcohol but also the environmental and sociocultural factors that influence patterns of alcohol consumption and violent behaviors [31].

Alcohol is a risk factor for the occurrence of violent acts because it has direct effects on physical and cognitive performances, contributing to violence by reducing self-control as well as reducing judgment and the ability to recognize signs of danger. Moreover, individual and cultural beliefs that alcohol causes aggression can lead to its intake in preparation or as an excuse/justification for violent acts [1]. It is also possible that harmful alcohol consumption is a coping strategy adopted by victims to address the stress caused by violent situations [1, 37].

Although strong associations seem exist between domestic violence and alcohol abuse among women, few studies have been conducted regarding the peculiarities of this association, especially in developing countries such as Brazil. Given this association, the WHO recommends measures to reduce the availability and the harmful consumption of alcohol as important strategies to prevent violence. There is some evidence on the success of brief interventions (BIs) in reducing various forms of violence, including domestic violence [1].

### Early detection and intervention for harmful alcohol consumption

The early detection of alcohol abuse is essential in preventing the future consequences of this consumption, because it enables the early application of interventions [38–40]. Given that many users do not recognize they have a problem in the early stages, interventions that allow problems to be recognized and behaviors to be changed become necessary.

BIs that are targeted on primary or secondary prevention strategies among alcohol consumers focus on changing an individual’s behaviors through limited-time therapies that can be performed by professionals with different backgrounds [39, 41]. Despite the variations in the forms of BIs application (e.g., in person, by phone, or online), the theoretical framework of motivational interviewing [42] and the principles of cognitive-behavioral therapy are usually employed.

Because BIs are an effective, low-cost strategy for treating problems related to alcohol and drugs, it is also a useful tool for prevention and a way to facilitate the referral of severe cases (e.g., those with alcohol dependence) to specialized treatments [38, 41, 43]. Previous studies have suggested that BIs work for different types of patients and that their effectiveness can be equal to or even better than those of interventions that require more time to complete [44]. Although BIs have been shown to be effective when performed by skilled professionals or researchers [41, 45], in clinical settings or in the context of routine health services, there is a lack of studies regarding the use of these techniques in community household settings. Such an approach should reach populations who do not have access to or choose not seek out the healthcare system; furthermore, it represents an alternative to the difficulties of implementing BIs in the healthcare services.

A comprehensive review of the BIs applied in primary care concluded that this approach decreases alcohol use among men; however, these findings were not extended to women. Therefore, additional research regarding the most effective components of such interventions is needed among this specific population [43]. Moreover, another literature review [46] identified promising results for women, despite the significant heterogeneity observed among the analyzed clinical trials. Because the evidence for the effectiveness of BIs remains contradictory among women [43, 46, 47], a well-conducted study that establishes the effectiveness of BIs is necessary for this population group, especially within developing countries. The assessment of BIs in community household settings is especially relevant in Brazil because this country has a strong strategy for primary health services that is focused on providing home care to families.

The current protocol is designed to study the association between alcohol consumption and patterns of domestic violence among women. Study 1 aims to (1) estimate the rates of harmful alcohol consumption and domestic violence (within the couple and that directed toward children) among adult women; (2) assess the association between the sociodemographic and mental health factors with regard to the harmful consumption of alcoholic beverages; and (3) assess the association between the sociodemographic and physical and mental health factors as well as between alcohol consumption and the occurrence of domestic violence (within the couple and that directed toward children).

Nested within Study 1, Study 2 aims to evaluate the effectiveness of BIs on women with harmful alcohol consumption living in a community household setting in reducing their alcohol consumption and patterns of domestic violence (within couples and toward children).

## Methods

### Study design

Study 1 will employ a cross-sectional observational design to investigate the patterns of alcohol consumption and domestic violence using a household survey of women. Study 2 will be a randomized clinical trial (RCT) nested within Study 1 (i.e., the women identified as having harmful alcohol consumption in Study 1 will be invited to take part in the RCT.

### Setting

The current study will be conducted in Juiz de Fora, Minas Gerais, southeastern Brazil; this city has approximately half a million inhabitants. The study will randomly select women living in two neighborhoods with different average monthly incomes per capita according to the Instituto Brasileiro de Geografia e Estatística (Brazilian Institute of Geography and Statistics; IBGE) census conducted in 2000. This categorization will be used to investigate two populations with different income profiles.

### Sampling

To calculate the sample size needed for this cross-sectional study, the data from a previous study (which estimated the prevalence of harmful alcohol consumption among women in Juiz de Fora as approximately 9.1 %) will be considered [48]. In addition, this study considered a maximum measurement error of 3 %, 95 % confidence intervals, a finite population correction based on the number of women residing in the randomly selected neighborhoods (consistent with the 2000 IBGE census), an effect of the sampling design equal to 2, and a 25 % refusal to participate rate. Thus, the initial sample size was estimated as 824 respondents (412 in each neighborhood).

To calculate the clinical trial sample size, the following considerations will be made: (i) a significance level of 5 %; (ii) a statistical power of 80 % (to compare proportions of the two independent groups); (iii) a non-interview rate of 15 % due to refusal to participate or failure to locate the informant; (iv) the effect of the BI after 3 months (i.e., an expected reduction of at least 20 % in the number of women with harmful alcohol consumption; and (v) an effect of the sampling design equal to 2. Thus, the calculated sample size for each group (i.e., the treated group [TG] and control group [CG]) will be 73 women.

To make the second study possible, considering the prevalence of women with risky alcohol consumption in the two neighborhoods surveyed around the estimated above (ie, 9.1 %), there will be necessary an increase in the sample size for Study 1, which now has approximately 1600, with 800 in each of the neighborhoods.

To recruit the women who belong to the target population, a two-stage cluster sampling method will be adopted. The streets belonging to each neighborhood will be considered as primary sampling units (PSUs), and households will be considered as secondary sampling units (SSUs). To select PSUs, a simple random sampling method without replacement will be adopted, whereas the SSUs will be selected using systematic sampling. In each selected household, the field researchers will invites all women who met the inclusion criteria to participate in the study.

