### Ethics

This study has been approved by Ethics Committee of the Federal University of São Paulo (Universidade Federal de São Paulo; UNIFESP- registration number 0699/10). The study has also been registered in the Brazilian Clinical Trials Registry (ReBEC; registration number: RBR-7rjt4t).

All participants will receive information about the study, and their participation will be voluntary. Each participant will be required to sign an informed consent document. At the end of the interviews, all participants will receive an informational leaflet regarding the use of alcoholic beverages, as well as a guide concerning health services and psychosocial assistance in cases of violence and alcohol dependence. After the follow-up assessment is performed three months after the screening, the BI will be applied to participants in the CG. Women who score in the range of “probable alcohol dependence” (i.e., 20 points or more on the AUDIT) will be instructed to seek specialized treatment, regardless of the group to which they are allocated.

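### The stated 80 % power rests on an unstated control proportion: with all five listed inputs, 73 per group implies that nearly every control still scores AUDIT ≥ 8 at 3 months

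*Protocol article*

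**What the plan says.** The Sampling section lists five inputs for the clinical trial:

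- (i) "a significance level of 5" %, with no statement of one- or two-sided;
- (ii) "a statistical power of 80 % (to compare proportions of the two independent groups");
- (iii) an allowance of 15 % for women who decline or cannot be found;
- (iv) for the brief intervention (BI), "the effect of the BI after 3 months (i.e., an expected reduction of at least", with the size then put at 20 % and counted over women who drink at harmful levels;
- (v) a design effect of 2.

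From these it concludes that "the calculated sample size for each group (i.e., the treated group [TG] and control group [CG]) will be 73 women". It gives no proportion for the control group (CG) at 3 months and does not say whether the 20 % is absolute or relative.

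Under Study 2 (Procedure), every randomised woman has an AUDIT score of 8 or more at entry, and the AUDIT is repeated in both groups after three months. Three other features bear on what controls will do:

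- Study design: "the women identified as having harmful alcohol consumption in Study 1 will be invited to take part in the RCT", so a positive screen is the route into the trial.
- Ethics: "all participants will receive an informational leaflet regarding the use of alcoholic beverages", together with a guide to health and psychosocial services.
- Ethics: women scoring 20 or more are told to seek specialised treatment whichever group they are in.

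**The concern.** A comparison of two independent proportions needs two proportions. The section supplies one reduction and no control value. Since all randomised women are positive at baseline, a 20 % reduction can easily be entered as a fall from 100 % to 80 % in the treated group (TG), with the CG left at 100 %.

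That is the most favourable choice available. A proportion of 100 % contributes no variance. Any improvement among controls adds variance and, if the 20 % is relative, also shrinks the difference. If the 80 % rests on that choice, a null result on this endpoint could be taken as evidence against the BI from an adequately powered comparison when the power was well below 80 %.

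**Working it through.** **Inputs.** Two-sided α = 0.05 (sidedness is my assumption), power 80 %, loss 15 %, design effect 2 and an effect of 20 %, all from the Sampling section. The control proportion p is not given, so it is varied. The treated proportion is q = p − 0.20 (absolute) or q = 0.80p (relative). The way the 15 % was applied is not stated, so both ×1.15 and ÷0.85 are shown.

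**Formula (unpooled).** n = (1.960 + 0.8416)² × [p(1−p) + q(1−q)] / (p−q)², with (1.960 + 0.8416)² = 7.849.

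**Reproducing 73.** For p = 1.00 and q = 0.80: 7.849 × (0 + 0.16)/0.04 = 31.4. Times 2 is 62.8. Then ×1.15 = 72.2 (rounds up to 73), or ÷0.85 = 73.9. Allowing a tolerance of 3 % around 73, the two-sided unpooled formula fits control proportions of about 99.6–100 %. The mirror case near 20 % v 0 % also fits arithmetically but is implausible for women who all start positive. The pooled formula at 100 % v 80 % gives about 80 (÷0.85) and does not reproduce the figure.

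**One-sided 5 %, all five inputs.** 98 % v 78 % pooled gives 72.6 (×1.15) or 74.3 (÷0.85); 97 % v 77 % unpooled gives 73.3 (×1.15).

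**Design effect left out, two-sided.** 90 % v 70 % pooled: 61.6/0.85 = 72.5. 88 % v 68 % unpooled: 63.4 × 1.15 = 72.9. 92 % with a relative 20 %, unpooled: 62.1/0.85 = 73.1. 93 % v 73 % with continuity correction: 73.4 (×1.15). These also reach about 73, but they contradict input (v).

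**Needed per group at lower control proportions.** Example at 90 %, all inputs, two-sided, unpooled:

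- absolute: 7.849 × (0.09 + 0.21)/0.04 = 58.9; ×2 = 117.7; ×1.15 = 135;
- relative: 7.849 × (0.09 + 0.2016)/0.0324 = 70.6; ×2 = 141.3; ÷0.85 = 166.

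**Power of 73 per group.** 73 × 0.85 = 62 analysed, and 62/2 = 31 effective at factor 2. Power = Φ(|p−q|/√([p(1−p)+q(1−q)]/n) − 1.96). Example at 90 % v 70 %, n = 31.0: 0.20/√(0.30/31.0) = 2.03; Φ(0.07) = 53 %.

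| Control still AUDIT ≥ 8 (assumed) | Needed per group, factor 2 | Power of 73, factor 2 | Power of 73, factor 1 |
|---|---|---|---|
| 100 % | 72–74 | 80 % | 98 % |
| 98 % | 86–91 | 71–72 % | 94–95 % |
| 95 % | 106–118 | 60–63 % | 88–90 % |
| 90 % | 135–166 | 46–53 % | 75–82 % |
| 80 % | 181–282 | 30–42 % | 52–70 % |
| 70 % | 208–430 | 21–38 % | 37–64 % |

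In the power columns the lower figure is the relative and the higher the absolute 20 %. At factor 1, power crosses 80 % at a control proportion of about 90 % (absolute) or 93 % (relative).

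**How far controls might fall by chance alone (illustration).** Assume a bivariate-normal latent score, 9.1 % above the cut-off and no true change. Then 77 %, 68 % or 55 % of women selected as positive remain positive on retest for test–retest correlations of 0.95, 0.90 or 0.80. The model and the correlations are not in the documents.

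**The case against.** The 100 % is back-calculated; the article never states it. Nor does it state the sidedness or the formula, and some of this may be in a fuller protocol. A reader might infer that 73 can arise only with every control still positive. That is too strong: a one-sided test with all five inputs fits at about 97–98 %, and ordinary control proportions of about 88–93 % fit two-sided if the design effect was listed but not used. The text cannot show which happened. It is equally not established that the 20 % was meant as a before–after change; the wording about the effect of the BI and two independent groups can be read as TG against CG.

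A reader might also infer that the power is lost as soon as one control improves, whatever the design effect. The table contradicts this. At factor 2 the decline is gradual, and at factor 1 power stays at or above 80 % until controls fall to about 90–93 %. The larger losses depend on charging a survey design effect against a comparison of individually randomised women, which is open to question.

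Finally, the Statistical analyses section compares the groups by t-tests and repeated-measures generalised linear models. Power for a dichotomised AUDIT is not the power of those analyses.

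All of this stands as a limit on the point. It does not remove it. The section presents 73 as following from five listed inputs, and those inputs deliver 80 % only with almost no improvement in controls. The alternative is that one listed input was not used, which would be a different error in the same calculation.

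**Conclusion.** The point holds in a bounded form. With all five listed inputs, 73 per group needs a 3-month control proportion of about 97–100 %, depending on sidedness. The protocol's own procedures make that doubtful: entry on a single score above a cut-off, a leaflet and service guide for all, and treatment advice for women scoring 20 or more in either group.

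At factor 2 and two-sided 5 %, the stated 80 % becomes 60–63 % at a 95 % control proportion, 46–53 % at 90 % and 30–42 % at 80 %. At factor 1 the claim survives down to about 90 % (absolute) or 93 % (relative) and then falls to 52–70 % at 80 %. All control proportions here are assumptions, the power figures are normal approximations, and they apply to the AUDIT ≥ 8 comparison only. The documents do not support saying that the authors assumed exactly 100 %.

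**What to change.** In the Sampling section:

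- define the 20 % as the TG minus CG difference in the proportion with AUDIT ≥ 8 at 3 months, and say whether it is absolute or relative;
- state the assumed control proportion, below 100 %, with its basis;
- state the sidedness and whether the design effect is applied to the between-group comparison;
- replace the unqualified 80 % by the power that 62 analysed women per group give over control proportions of about 70–95 %.

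The cost is a recalculation and a few lines of text. No extra enrolment follows from it. The downside is a less favourable stated power.

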#### Study 2: Random clinical trial

The data collection for Study 2 will be conducted concomitantly using the women detected in Study 1. Women with AUDIT scores equal to or above 8 will be considered as hazardous alcohol users and randomly allocated into one of two groups: the TG or the CG. The TG will receive a single BI after the instrument is administered, whereas the CG will not receive BI until after the end of the study.

The participants will be allocated using a list of random numbers. Three months after the BI, all instruments except for the sociodemographic questionnaire will be re-administered to both groups. Because of ethical reasons, a BI session will also be offered to the CG after the second evaluation, at the end of the study. Independent interviewers will perform the baseline and the follow-up interview.

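### The 73 women per group for 80 % power is reproduced essentially only if almost no control improves, so the stated power is too favourable as written

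*Protocol article*

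**What the plan says.** The Sampling section lists five inputs for the clinical trial:

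- "a significance level of 5" %, with sidedness not stated;
- "a statistical power of 80 % (to compare proportions of the two independent groups";
- "a non-interview rate of 15 % due to refusal to participate or failure to locate the informant";
- "an expected reduction of at least 20 % in the number of women with harmful alcohol consumption", at three months;
- "an effect of the sampling design equal to 2".

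The result is 73 women in each of the treated and control groups. No three-month proportion is given for the control group.

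Three statements elsewhere bear on that proportion. Under Study 2, "Women with AUDIT scores equal to or above 8 will be considered as hazardous alcohol users and randomly allocated into one of two groups", so every woman is above the cut-off at entry. Under Ethics, "all participants will receive an informational leaflet regarding the use of alcoholic beverages", and women scoring 20 or more "will be instructed to seek specialized treatment, regardless of the group to which they are allocated".

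**The concern.** A comparison of two independent proportions needs both proportions. If the missing one was set at or near 100 %, the calculation takes an expected fall from entry in the treated group as though it were the difference between the groups. That holds only if controls do not change.

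The protocol gives three reasons to expect some change. Women enter because of a single screening score above a cut-off, and some will fall below it on retest without any intervention. Controls receive alcohol information. Controls in the top AUDIT band are advised to seek treatment.

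At stake is how a null result is read. The Background justifies the trial by the contradictory evidence on brief interventions in women. A null finding from a trial believed to have 80 % power would count for more than it should if the real power were lower.

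**Working it through.** **Reproducing 73.** Take a two-sided 5 % test (z = 1.96), 80 % power (z = 0.8416) and the unpooled formula:

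n = (1.96 + 0.8416)² × [p1(1−p1) + p2(1−p2)] / (p1−p2)²

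With p1 = 1.00 (control) and p2 = 0.80 (treated): n = 7.849 × 0.16 / 0.04 = 31.4. Multiplying by the design effect, 31.4 × 2 = 62.8. Multiplying by 1.15 for non-interview, 62.8 × 1.15 = 72.2, which rounds up to 73. Dividing by 0.85 instead gives 73.9, so 74.

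**Is another control rate compatible?** The same chain (design effect 2, × 1.15) for a 20-point difference gives:

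| Control v treated | n before inflation | n per group |
|---|---|---|
| 100 % v 80 % | 31.4 | 72.2 |
| 95 % v 75 % | 46.1 | 106.1 |
| 90 % v 70 % | 58.9 | 135.4 |
| 80 % v 60 % | 78.5 | 180.5 |
| 70 % v 50 % | 90.3 | 207.6 |

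A search over control rates from 1 to 100 %, with the reduction absolute or relative, finds one other two-sided match. It is the arithmetic mirror, 20 % v 0 %, which would need 80 % of controls to improve and no treated woman to remain positive. A one-sided test reaches about 73 at control rates of roughly 96 to 98 %. The pooled formula at 100 % v 80 % gives about 79 to 81. A near-100 % control rate is therefore the only plausible source of the figure.

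**Power if controls improve.** After 15 % loss, 73 × 0.85 = 62 women per arm are analysed. With the stated design effect, 62 / 2 = 31 are effective. With p̄ the mean of p1 and p2, and the pooled-variance formula:

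power = Φ{ [ |p1−p2|√n − 1.96√(2p̄(1−p̄)) ] / √(p1(1−p1) + p2(1−p2)) }

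Example, 90 % v 70 %, n = 31: (0.2 × 5.568 − 1.96 × 0.5657) / 0.5477 = 0.01, so power is 50 %. With n = 62: (0.2 × 7.874 − 1.1087) / 0.5477 = 0.85, so power is 80 %.

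The document gives no control rate, so those below are assumptions.

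| Control rate | 20 points absolute, n = 31 | 20 points absolute, n = 62 | 20 % relative, n = 62 |
|---|---|---|---|
| 95 % | 60 % | 89 % | 86 % |
| 90 % | 50 % | 80 % | 73 % |
| 80 % | 40 % | 69 % | 51 % |
| 70 % | 36 % | 63 % | 36 % |

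At n = 31 the unpooled formula gives slightly more: 63 %, 53 %, 42 % and 38 % (20 points absolute).

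**Which n applies.** The design effect of 2 comes from a two-stage sample of streets and households. Study 2 allocates individual women from a list of random numbers, so street clustering is shared by both arms and does not by itself double the variance of their difference. The n = 62 columns are therefore the fairer account of what the trial can do. The n = 31 column shows what the printed inputs imply.

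**Detectable difference.** With 62 analysed per arm and 80 % power, the absolute difference is about 20, 23 and 25 points at control rates of 90, 80 and 70 %.

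**The case against.** The strongest reply is that the two questionable inputs work in opposite directions. Once the survey design effect is taken out, 62 women per arm keep 89 % power at 95 % v 75 % and 80 % at 90 % v 70 %. A reader might infer that any improvement among controls destroys the stated power, or that the trial could not have detected a 20-point difference. The documents support neither. On the absolute reading, power reaches 80 % until about one control in ten improves. Below that it is reduced (69 % and 63 % at control rates of 80 and 70 %), not absent. The plan also expects a reduction of at least 20 %, so a larger true effect would have more power.

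The 100 % control rate is a back-solved inference. The article states neither the formula, the sidedness nor the form of the loss adjustment, and an exact 73 needs the unpooled formula with multiplication by 1.15. This is a fair caution, but every plausible variant that keeps the listed inputs and comes near 73 has a control rate close to 100 %.

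An article may leave the control proportion to a fuller document, so its absence alone is not the defect. The defect is that the printed inputs and result fit together only at an extreme value that the design makes unlikely. How far controls will improve cannot be taken from the document.

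Finally, the Statistical analyses section compares the groups by t-tests and repeated-measures generalized linear models. Power for a dichotomised AUDIT does not settle what a null result on those analyses would mean. That limits the consequence but does not rescue the stated figure.

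**Conclusion.** Wrong as written, and should be fixed. With the printed inputs, 73 per group corresponds to 80 % power essentially only if nearly all controls remain at AUDIT 8 or above at three months. If controls improve, those same inputs give about 60 %, 50 % and 40 % power at control rates of 95, 90 and 80 %. With the survey design effect removed, the shortfall is smaller. Power is about 80 % or better at control rates of 90 % and above for an absolute 20-point difference, and falls short below that. On a relative reading it already falls short at 90 % (73 %), with 51 % and 36 % at 80 and 70 %.

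These figures assume a two-sided 5 % test, 15 % loss, the pooled-variance power formula and the assumed control rates. A null result may reflect inadequate power; the documents do not show that it must.

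**What to change.** Keep 73 per group and rewrite the trial part of the Sampling section:

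1. State the assumed three-month proportion of controls at AUDIT 8 or above, as a range and labelled as an assumption.
2. Say whether the 20 % is an absolute or a relative difference between the groups, and give the sidedness, formula and loss adjustment.
3. Drop the survey design effect from the randomised comparison, or justify it for individually allocated women.
4. Replace the single 80 % with power, or the detectable difference, over the stated range. With 62 analysed per arm the detectable difference is about 20, 23 and 25 points at control rates of 90, 80 and 70 %.

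The cost is a rewritten paragraph and a less favourable power statement. No further women are needed, and the design and analysis do not change.
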